### Setting, Study Population, and Sample Size

The study will be conducted in 3 group practices of GPs in the southeast of the Netherlands, where 18 GPs provide primary care to approximately 22,000 patients. This setting is a pragmatic choice based on the health information system that is used in these practices and the willingness of the GPs to provide Web-based access to their records and to participate in this study. Assuming that uptake, use, and effects will differ among different groups of patients, we will recruit a random sample from three groups of patients: (1) adult patients using five or more different types of medication (polypharmacy patients), (2) parents of children aged <4 years, and (3) other adult patients (those who do not belong to the first two groups). Both polypharmacy patients and parents of young children are frequent users of GP services, with an expected number of 5 and 2 contacts, respectively, with the GP during the 6-month study period [39]. They are likely to differ in terms of health status, age, internet use, and computer skills. Patients aged >75 years and those with severe cognitive or psychiatric problems will be excluded; furthermore, patients for whom access to the records may be harmful to themselves or others according to the GPs will be excluded.

Because of the lack of available figures, a proper power analysis to determine the sample size is not feasible. However, we expect that a sample of 50 users and 100 nonusers of the PHR in each group will be suitable for our aims. We assume that the uptake of the intervention will be approximately 10%, based on experiences in these practices along with the adoption rates of other eHealth interventions and based on the adoption rates of these services in the Netherlands [16]. With an expected participation rate of 25%-50% for research using questionnaires in general practice in the Netherlands [40,41] and an assumed uptake of the intervention of approximately 10% and taking into account that GPs may exclude some patients, we will use a random sample of 550 patients for each group for the quantitative study: 550 polypharmacy patients, 550 parents of children aged <4 years, and 550 other patients.

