### Recruitment Procedure and Informed Consent

Eligible patients will be invited to participate in the study to create a profile on MijnZorgnet and to sign up for Web-based access to the summary of their GP records. They will receive an invitation letter signed by their GP along with the study brochure and a consent form. In the invitation letter, a code will be included that patients can use to open the first digital questionnaire. The first page of this questionnaire is a consent form. If patients indicate on this page that they do not consent to participate, they will not be able to complete the questionnaire. In the first questionnaire, patients will be asked whether they are willing to participate in the qualitative study strands. We will send a reminder after 3 and 6 weeks to all patients who have not used the code in the invitation letter.

All patients who attend a focus group session or who are interviewed or observed during the think-aloud sessions will be asked to sign a consent form at the beginning of the session. Similarly, the GP staff will be asked to sign consent forms.

To sign up for Web-based access to the summary of their GP records, patients will need to go to the GP practice to hand-in the consent form for Web-based access to their records and for identification. Subsequently, they will receive an email with a link to the PHR and a link to activate the connection between the PHR and the summary of the GP record.

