### Analysis

#### Analysis of Quantitative Data at the Patient Level

Descriptive statistics will be used to describe the characteristics of the users and nonusers for each group of participants. To assess whether nonusing and using responders are representative of polypharmacy patients, parents of young children, and other patients in the 3 practices, we will compare their characteristics with those of the population they were obtained from using two sample *t* tests for continuous variables and chi-square tests for categorical variables. We will perform multiple linear regression analyses to investigate the effects of age, sex, education level, perceived health, health literacy, and internet and eHealth use on the adoption of the PHR and access to the summary record, defined as having logged in at least once to the PHR and the summary record. We will use descriptive analyses for data derived from the questionnaires about perceived usefulness, experiences, opinions, and concerns and for log in data on the number of days (hit days) the users have accessed their GP records and viewed different parts of the records during the study period. For each group of patients, we will compare the means changes in in-person levels of playing an active role in decision making and in the management of condition and medication adherence over the 6-month study period between users and nonusers using two sample *t* tests. Similarly, we will analyze the secondary outcomes. We will use a *P* value <0.05 (two sided) as a criterion for statistical significance for all analyses. Because of the explorative character of our study, we will not correct for multiple testing using a more stringent *P* level. We will deal with the problem regarding multiple testing in the interpretation of results by primarily focusing on the primary outcomes and by integrating the qualitative findings with the results of quantitative comparisons. SPSS Statistics software (IBM Corp, Armonk, NY, United States) will be used for the analyses.

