### Strengths and Limitations

Our protocol has some strengths and limitations. We consider the use of a clear conceptual framework as a strength of the study, even though drawing on two theories (the Unified Theory of Acceptance and Use of Technology and Snyder’s model on patient involvement), it is a rather complex framework [1,25]. This framework has helped us include all variables that are likely to be relevant to our study, and it will also guide the interpretation of findings. The mixed-methods design enables us to assess the uptake and potential effects and obtain a deeper understanding of the use and nonuse of the intervention and the effects or absence of the effects [32]. Another strength is that we will conduct the study at two levels, patient level and GP staff level. GP staff is likely to influence the use and impact of the intervention among patients. Because the relationship between patients and GP staff may change due to the intervention, it is important to obtain information from both patients and GP staff. Another strong point of this study is the use of validated instruments to assess the effects of the intervention. However, these instruments have not been validated among parents of young children. Therefore, we will need to interpret the results based on the questionnaires on the effects on involvement-related outcomes in parents with great care. Multiple testing may be another limitation of our study. We will deal with this in the interpretation of our results by focusing on the primary outcomes and aligning qualitative findings with the results of the comparisons. We will conduct this study in the practices of GPs who are open to innovation and willing to provide their patients access to their records. We are aware that this setting is not representative of Dutch general practice. In addition, we are aware that our findings about adoption will need to be interpreted with caution because our participants, particularly those who take part in the focus group discussions, think-aloud observations, or semistructured interviews, will receive more information about the PHR and its use, than is likely to occur in a real-life setting. Furthermore, we realize that not including patients older than 75 years may also influence our findings. Obviously, we will take this into account during the interpretation of our results.

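### Practice is absent from the adoption model and the user-nonuser comparisons of change, so differences between the three practices, if there are any, may be read as patient predictors or as effects of use

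*Protocol article*

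**What the plan says.** The section Analysis of Quantitative Data at the Patient Level names the terms of the adoption analysis one by one: "the effects of age, sex, education level, perceived health, health literacy, and internet and eHealth use on the adoption of the PHR". Practice is not listed. For the involvement outcomes and medication adherence, the same section compares mean within-person change, separately in each patient group, "over the 6-month study period between users and nonusers using two sample" t tests, and treats the secondary outcomes likewise. It mentions neither adjustment for practice nor stratification by it.

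Other sections describe how the intervention reaches patients:
- Setting, Study Population, and Sample Size gives the location and scale: "The study will be conducted in 3 group practices of GPs in the southeast of the Netherlands, where 18 GPs provide primary care".
- Recruitment Procedure and Informed Consent: to get access to the record, "patients will need to go to the GP practice to hand-in the consent form for Web-based access to their records and for identification". The invitation letter carries the GP's signature.
- The intervention section: questions about what the summary record contains go to practice staff.
- Conceptual Framework: the GP support that patients perceive counts as a social influence on uptake.
- Strengths and Limitations: "GP staff is likely to influence the use and impact of the intervention among patients".

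**The concern.** Adoption predictors and change in involvement are both primary outcomes. User status is the grouping variable for the second and the dependent variable for the first. Invitation, sign-up and follow-up questions all run through the practice, so practice could plausibly be related to who becomes a user. Patient mix, or the average change over six months, may also vary between practices. If so, a pooled analysis cannot separate the practice from the patient trait or from use.

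With only three practices, one active practice could supply a large share of the users. At stake is a regression coefficient reported as a patient predictor, or a t test reported as an effect of access, that partly reflects where the patient is registered.

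**Working it through.** **1. The plan's own figure.** The target is 50 users and 100 nonusers per patient group. Uptake of 10% applied to 500 invited patients (the abstract's number) gives 50 users. Participation of 25%-50% gives 125-250 respondents, which leaves 75-200 nonusers and so covers 100. The target is reproduced, and it implies a user share among analysed patients of 50/150 = one third. No practice-level figure, SD or intraclass correlation is given, so every practice contrast below is an assumption.

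**2. User-nonuser comparison of change.** Take three equal practices with user shares p_k and mean changes m_k (in SD units) that apply to users and nonusers alike, so use has no effect. Then

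bias = Σ m_k (u_k − n_k), with u_k = p_k/Σp and n_k = (1 − p_k)/Σ(1 − p).

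Example: p = 1/6, 1/3, 1/2 and m = −0.25, 0, +0.25. Here u = 0.167, 0.333, 0.500 and n = 0.417, 0.333, 0.250. The bias is 0.25 × (0.500 − 0.167) − 0.25 × (0.250 − 0.417) = 0.083 + 0.042 = 0.125 SD.

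Type I error at a two-sided 0.05 level was simulated with 150 patients and 4,000 runs per row. The Monte Carlo standard error near 5% is √(0.05 × 0.95/4000) = 0.3 percentage points.

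| User share by practice | Mean change by practice (SD) | Bias (SD) | Type I, t test | Type I, practice added |
|---|---|---|---|---|
| 33/33/33% | −0.5/0/+0.5 | 0 | 4.4% | 4.8% |
| 17/33/50% | 0/0/0 | 0 | 5.1% | 4.9% |
| 25/33/42% | −0.1/0/+0.1 | 0.025 | 5.3% | 5.0% |
| 25/33/42% | −0.25/0/+0.25 | 0.063 | 6.4% | 5.0% |
| 17/33/50% | −0.25/0/+0.25 | 0.125 | 11% | 4.9% |
| 17/33/50% | −0.5/0/+0.5 | 0.25 | 27% | 4.9% |
| 10/30/60% | −0.5/0/+0.5 | 0.375 | 53% | 5.1% |

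The first two rows show that a difference in only one of the two quantities gives no bias. Across all scenarios run, the model with practice stayed between 4.8% and 5.1%.

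**3. Adoption model.** Assume uptake of 5/10/15%, low education in 40/30/20% of patients, and no education effect inside any practice.
- Low education: (0.4×0.05 + 0.3×0.10 + 0.2×0.15)/0.9 = 0.08/0.9 = 8.9%.
- Higher education: (0.6×0.05 + 0.7×0.10 + 0.8×0.15)/2.1 = 0.22/2.1 = 10.5%.
- Spurious difference: 1.6 percentage points. Odds ratio: (0.0889/0.9111)/(0.1048/0.8952) = 0.83.

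With the same uptake, a milder or steeper gradient in the trait (25/30/35% or 10/30/50%) gives 0.8 or 3.2 points in absolute size. The effect is zero if uptake or the trait is equal across practices.

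A 10% base does not match the data that will be analysed. Education comes from the baseline questionnaire, so only respondents enter the model, and the target user share among them is one third. The same threefold gradient on that base is 16.7/33.3/50%:
- Low education: (0.4×0.167 + 0.3×0.333 + 0.2×0.5)/0.9 = 0.267/0.9 = 29.6%.
- Higher education: (0.6×0.167 + 0.7×0.333 + 0.8×0.5)/2.1 = 0.733/2.1 = 34.9%.
- Difference: 5.3 points. Odds ratio: (0.296/0.704)/(0.349/0.651) = 0.78.

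The standard error with 150 patients (45 low, 105 higher) is √(0.333×0.667×(1/45 + 1/105)) = 0.084, so z = 0.053/0.084 = 0.63 and the spurious difference reaches p < 0.05 in about 10% of studies. With 450 patients (three groups pooled) the standard error is 0.0485, z = 1.09 and the chance about 19%. On the 10% base the corresponding chances are about 6% and 8%.

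**The case against.** A reader might infer that delivery differs between practices and that practice differences will therefore be taken for predictors and effects. The documents do not support that. They describe one procedure throughout: the same GP-signed letter and brochure, the same reminders, the same sign-up step and the same help desk. All three practices were chosen for their information system and their GPs' willingness, which may make them more alike. The statement about staff influence does not say that the influence varies by practice. Influence on the impact of the intervention would also, strictly, make the effect of use vary by practice; the bias worked out here needs mean change to differ by practice apart from use. This part of the objection stands, and it is why the point is conditional.

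It can also be said that the listed predictors need not be the full adjustment set, and that a condensed article may leave centre terms to a fuller document. That has some force for the adoption model. It has little for the change comparisons, because a two-sample t test is named and cannot carry a practice term.

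Finally, the study is exploratory, each practice has a staff focus group, and the staff findings are meant to complement the patient results. These can help to explain a practice difference but cannot take it out of a coefficient or a mean difference.

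**Conclusion.** The point holds in a conditional form. The stated analyses leave out practice, while the protocol's own account makes practice a plausible source of confounding. Bias arises only if practices differ in uptake and also in predictor mix (adoption model) or mean change (t tests). The documents neither show nor exclude this.

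Under modest assumed differences the effect is negligible to small: 0.025-0.063 SD, with type I error of about 5%-6%. It becomes material only with large, aligned differences: 0.125-0.375 SD, with type I error of 11%-53%. These figures rest on equal practice sizes, 150 analysed patients and a one-third user share. They illustrate a range and are not estimates for this study. The case for acting rests mainly on the low cost of the remedy.

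A reader should also not infer that adjusting for practice would turn the user-nonuser contrast into a causal effect. Patients choose whether to become users, and that self-selection remains.

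**What to change.** - Add practice as a fixed factor (three levels, two indicators) to the adoption model. Three practices are too few for a reliable random effect.
- Within each patient group, replace the t test of change with a linear model of change on user status plus practice, or report that model beside the t test. Do the same for the secondary outcomes.
- Report sign-up and adoption by practice, so that readers can see whether the condition for bias is met.

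The cost is two degrees of freedom per model (146 instead of 148 residual with 150 patients) and a little more analysis, because the t tests have to be recast as regressions. No new data collection should be needed, since patients are sampled from the practices and sign up there.

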#### Analysis of Qualitative Data at the Patient Level

Focus group discussions, think-aloud observations, and semistructured interviews will be transcribed verbatim. Using the ATLAS.ti software (ATLAS.ti Scientific Software Development GmBH, Berlin, Germany), two researchers will code the data independently using open coding as well as coding within the predetermined topics: barriers and facilitators for uptake as well as concerns about privacy and security, usability, usefulness, benefits, and disadvantages. Within the topic usability, we will explore the accessibility of the system and ease to navigate through the PHR and the summary of the GP records. We define usefulness of access to the summary records as the understandability, credibility, and desirability of the information that was viewed. We consider usefulness of the PHR as the extent to which patients value the functionalities to store and share information through the PHR. We consider benefits as positive experiences resulting from the use of the PHR and accessing the summary record. The codes will be categorized into themes that will be defined by the research team in an iterative process. Using the framework approach for the analysis of qualitative data [69,70], we will search for patterns that we will use to complement and interpret our quantitative findings on fidelity, dose, reach, and effects.

#### Analysis of the Qualitative Data at the General Practice Staff Level

The focus group discussions with the GP staff will be transcribed verbatim and coded independently by two researchers. In an iterative process, the codes will be categorized and the themes and subthemes and potential patterns will be distinguished. We will analyze the Q-sorts using the PQMethod software (PQMethod, GNU GPL, Peter Schmolck, Munich, Germany). To identify the shared views among the groups who ranked the statements similarly, a by-person factor analysis of the Q-sorts will be performed. Of each of the resulting factors, a composite Q-sort will be produced, representing the ranked statements of a hypothetical person with a 100% factor loading on this factor. Two researchers will analyze the composite Q-sorts (factor arrays), comparing the statements that are ranked in the extremes of the grids and in the more neutral positions between the different factor arrays. Together, they will interpret identified shared views between certain groups of participants. The results of the focus group analysis and Q-methodology analysis will be used to complement findings at the patient level.

### Ethical Approval

Ethical approval has been requested and granted under file number 2016-2942 by the research ethics committee of the Radboud University Nijmegen Medical Center based on the Dutch Code of Conduct for Health Research, the Dutch Code of Conduct for Responsible Use, the Dutch Personal Data Protection Act, and the Medical Treatment Agreement Act.

## Results

Enrollment was completed in May 2017 and the possibility to view GP records through the PHR was implemented in December 2017. Data analysis is currently underway and the first results are expected to be submitted for publication in autumn 2019.

## Discussion

### Relevance

In this paper, we have described the protocol for studying patient access to GP records through a standalone PHR. To obtain a comprehensive understanding of the effects of this complex intervention, we designed a mixed-methods study of patients in general practice and GP staff, allowing us to assess the facilitators and barriers for the adoption of the intervention, actual use (reach, dose, and fidelity) of the intervention, and experiences and effects on patient involvement. To the best of our knowledge, this is the first study in the Netherlands to investigate patient Web-based access to summary records and use of a PHR in general practice. In addition, few studies on this topic have been carried out in Europe [71-74]. The uptake and effects of and experiences with Web-based access to medical records have been explored more extensively in the United States [26,36,75,76]. However, because the barriers and facilitators for the uptake and effects of Web-based access to medical records are likely to be determined using different factors, including social and cultural, the findings from studies conducted in the United States may not be applicable to the European context.

### Strengths and Limitations

Our protocol has some strengths and limitations. We consider the use of a clear conceptual framework as a strength of the study, even though drawing on two theories (the Unified Theory of Acceptance and Use of Technology and Snyder’s model on patient involvement), it is a rather complex framework [1,25]. This framework has helped us include all variables that are likely to be relevant to our study, and it will also guide the interpretation of findings. The mixed-methods design enables us to assess the uptake and potential effects and obtain a deeper understanding of the use and nonuse of the intervention and the effects or absence of the effects [32]. Another strength is that we will conduct the study at two levels, patient level and GP staff level. GP staff is likely to influence the use and impact of the intervention among patients. Because the relationship between patients and GP staff may change due to the intervention, it is important to obtain information from both patients and GP staff. Another strong point of this study is the use of validated instruments to assess the effects of the intervention. However, these instruments have not been validated among parents of young children. Therefore, we will need to interpret the results based on the questionnaires on the effects on involvement-related outcomes in parents with great care. Multiple testing may be another limitation of our study. We will deal with this in the interpretation of our results by focusing on the primary outcomes and aligning qualitative findings with the results of the comparisons. We will conduct this study in the practices of GPs who are open to innovation and willing to provide their patients access to their records. We are aware that this setting is not representative of Dutch general practice. In addition, we are aware that our findings about adoption will need to be interpreted with caution because our participants, particularly those who take part in the focus group discussions, think-aloud observations, or semistructured interviews, will receive more information about the PHR and its use, than is likely to occur in a real-life setting. Furthermore, we realize that not including patients older than 75 years may also influence our findings. Obviously, we will take this into account during the interpretation of our results.

### Implications for Clinical Practice or Further Research

We expect this proof-of-principle study to be useful for policy makers, patient organizations, and HCPs who want to increase patient-centered care and patient involvement through PHRs or portals that provide patients access to medical records. Further research will be necessary to assess the uptake, use, and effects of patients’ access to different parts of their medical records using PHRs on their health outcomes in various European settings.

